**6.19 Training**

The data collectors will be trained by the principal investigators study aim and objectives, roles and responsibilities, research ethics, and interviewing skills. The role plays and demonstration of the interviewing skills will be carried out among the enumerators to improve the interviewing skills and how to record the respondent’s response on the questionnaires.

Three days of training will be provided to qualitative data collectors on moderation skills, the FGD guide, and the interview guide. Demonstration and role play will be an integral part of the training.

Three-day training will be provided to health extension workers by the researcher. The training contents will be based on WHO gender-based violence prevention guidelines, and they are adapted to violence against women education for health extension workers. The health education content for male partners is also included. The training will cover

- Gender-based violence
- Violence against women
- Intimate partner violence
- Types of intimate partner violence (physical, sexual, and psychological or emotional violence)
- Magnitude of intimate partner violence in pregnancy
- Inequitable gender norms and consequences
- The relationship between intimate partner violence and power and control
- Common triggers of IPV in pregnancy
- Uhhealthy and healthy relationship
- Common triggers of IPV and ways to challenge the triggers
- Effective communication and conflict resolution in relationship

**6.20 Research Team**

The research team for this study consists of a principal investigator and three supervisors.

**6.21 Data collection instruments**

**Questionnaires**

**Quantitative study**: structured-interviewer-administered questionnaires adapted from the WHO multi-country study questionnaire will be used to collect information on intimate partner violence in pregnancy (WHO, 2010). The English version of the questionnaire will be translated into the local language (Hadiyisa) by fluent speakers. Then, the questionnaire's local language will be translated back to English by another expert to ensure consistency and accuracy. Four types of questionnaires will be administered at baseline and at the endline for couples (pregnant wife and husband). The data will be collected using a mobile-based application called KoBo Collect. The content of the information under each questionnaire will be as follows:

**Questionnaire for pregnant mothers at baseline and end-line**: the questionnaire will be administered to all pregnant women in the two groups (intervention and control groups) after obtaining informed verbal and written consent. The questionnaire contains individual characteristics of mothers, including age, levels of education, occupation, marriage type, parity, pregnancy intention, and household characteristics. Relational characteristics: duration of marriage and disparity in educational attainment

Moreover, the relational characteristics include the presence of social support and religion. The societal characteristics of pregnant women include women’s autonomy in addition to male involvement in antenatal care. All questionnaires will be administered to the intervention and control groups before any education session. Outcome measures: couples' knowledge, attitude, and control towards IPV; self-efficacy; pregnant women’s experience of IPV in the last 12 months and during the recent pregnancy

**Questionnaire for husbands at baseline and end-line:** similarly, these questionnaires will be administered to husbands of pregnant women in two study groups. The questionnaire consists of information in terms of male partners individual characteristics, including age, levels of education, religion, occupation, marriage type, current alcohol use, current smoking status, women’s autonomy, self-efficacy, and household characteristics. Relational characteristics include the duration of marriage and disparity in educational attainment; community characteristics include the presence of social support. The societal characteristics of male partners include also decision-making power outcome measures such as partner’s knowledge, attitude, and control towards IPV.

**Focus Group Discussion (FGD) guides:** The guide will be used during FGD to collect qualitative information on male partners perspectives towards intimate partner violence, awareness and consequences of IPVs, risk and protective factors of IPV in pregnancy, and myths and misconceptions about intimate partner violence. Themes will be followed by several probes and questions to get a deep insight into the perpetration of IPV. The group discussion may take 60–90 minutes. Besides, the interview guides, tape recorder, and note book will be used during FGDs.

**6.22 Data Quality Control**

To assure the quality of the data, data collectors and supervisors will be trained thoroughly for 3 days. Regular supervision and follow-up will be provided by supervisors and the principal investigator, respectively. In addition, a regular check-up for the completeness and consistency of the data will be made on a daily basis. Every day, collected data by Kobo Collect will be sent to the server (KoKo Toolbox). The questionnaire will be translated into an Amharic version and then back to English by translators who are blind to the original questionnaire. To make the questionnaire standard, reliability and validity tests will be done for items of intimate partner violence, women’s autonomy and self-efficacy, knowledge, attitude, and controlling behavior towards IPV. A pre-test will be carried out in the kebele that will not be included in the actual study in order to validate and standardize the study procedure and research tools.

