## 6.16 questionnaire translation, validity and reliability

**Quantitative data**: An essential step for the questionnaire's validity is the translation of the original English version into a native language (Wild et al., 2005). We'll follow a methodical procedure suggested by Beaton et al. (Dorcas E. Beaton, 2000) to maintain conceptual, experiential, and idiomatic equivalence. Bilingual translators will translate the instruments into Hadiyisa. The instruments will be translated back into English by two bilingual translators from the Department of Hadiyisa, Wachemo University, who are completely blind to the original English version. To establish semantic equivalence, the back-translation is necessary. To combine all language versions and create the pre-final questionnaire for field testing, an expert committee meeting will be organized (Abdulahi et al., 2018). To verify the translation's accuracy, the original and back-translated English versions of the instruments will be compared. Using a technique developed by Skperber et al. (Sperber et al., 2016), each item in the original and back-translated versions will be ranked in terms of comparability of language and similarity of interpretability for the purpose of certifying the translated instrument. Fluent in English experts from the department of foreign languages and literatures will assess the comparisons using Likert scales from 1 (highly comparable/extremely similar) to 7 (not at all comparable/not at all similar). There will be a formal evaluation of the translation for any mean score greater than 3.

Pilot testing of the translated tool will be conducted among 27 couples who will not be included in the actual trial to assess its understanding, comprehension, and appropriateness. Additionally, subject experts will evaluate the content, and the necessary changes will be made (Figure 8). The tools' internal consistency will be tested using Cronbach's alpha. A tool with a Crombach alpha of ≥ 0.7 will be considered reliable(Sharma, 2016). Finally, the questionnaires will be utilized at the study's baseline and completion.

Content Validity

(IPVp)

Forward translation by public health experts /group-1

Forward translation by Language experts/group-2

Backward translation by

Public health experts/group-3

Backward translation by language experts /group 4

Review of 4 version of the questionnaire and final versison (IPVp)

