**Annex VI: የአማርኛ መጠይቅ (የምስት)**

**መልሱን የያዘውን ፊደል በማክበብ ምረጡ ወይንም ክፍት ቦታውን የምሰጡትን ምላሽ በመጻፍ አሟሉ**

| **ክፍል አንድ፡ የግለሰብ፣ ግንኙነት፣ የማህበረሰብ እና የማህበረሰብ ደረጃ መጠይቆች** | | | |
| --- | --- | --- | --- |
| መለያ  ቁጥር | ጥያቄዎች | አማራጭመልስ | እለፍ |
| 101 | አሁን ዕድሜዎ ስንት ነዉ? | ሙሉ ዓመት…………….……… |  |
| 102 | ወደ ጋብቻ ስገቡ ዕድሜዎ ስንት ነበር? | ሙሉ ዓመት በቁጥር……………. |  |
| 103 | የሚኖሩበት ቦታ የት ነዉ? | ገጠር……………………………………….…1  ከተማ…………………………………………2 |  |
| 104 | ከተጋቡ ምን ያህል ዓመት ቆይተዋል? | ሙሉ ዓመት………………………………..1  አላዉቅም----------------------------------2 |  |
| 105 | የባሎት ዕድሜ ስንት ነዉ? | ሙሉ ዓመት _________________ |  |
| 106 | ሀይማኖትዎ ምንድነዉ? | ጴንጤ.................................................................1  ኦርቶዶክስ.........................................................2  ሙስሊም...............................................................3  ካቶሊክ..... ........................................................4  ሌላ ይገለጽ............................................................5 |  |
| 107 | የባሎት ሀይማኖት ምንድነዉ? | ኦርቶዶክስ.............................................................2  ሙስሊም.........................................................3  ካቶሊክ..... ............................................................4  ሌላ, ይገለጽ........................................................5 |  |
| 108 | ብሄሮት ምንድነዉ ነዉ? | ሀዲያ.................................................................1 ክምባታ...........................................................2  ስልጤ................................................................3  ጉራጌ.................................................................4  ሌላ, ይገለጽ......................................................5 |  |
| 109 | የባሎት ብሄር ምንድነዉ ነዉ? | ሀዲያ.................................................................1 ክምባታ...........................................................2  ስልጤ................................................................3  ጉራጌ.................................................................4  ሌላ, ይገለጽ......................................................5 |  |
| 110 | የትምህርት ደረጃዎት ስንት ነው? | ትምህርት የለም.................................................1  አንደኛ ደረጃ ትምህርት ቤት (1-8)......................2  ሁለተኛ ደረጃ ት/ቤት (9-12)………………..….3  ኮሌጅ ወይም ከፍተኛ ትምህርት ተከታትሏል …...4 |  |
| 111 | የባሎት የትምህርት ደረጃ ስንት ነዉ? | ትምህርት የለም.................................................1  አንደኛ ደረጃ ትምህርት ቤት (1-8)......................2  ሁለተኛ ደረጃ ት/ቤት (9-12)………………..….3  ኮሌጅ ወይም ከፍተኛ ትምህርት ተከታትሏል …...4 |  |

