**Annex vii: የባሎች መጠይቅ -አማርኛ ትርጉም**

መጠይቁ የተሞላበት ቀን (በኢት. አቆጣጠር)------------

የመጠይቅ ቁጥር--------------------

የጠያቂ መለያ ቁጥር-----------------

መጠይቁ የተጠየቀበት ቀበል-----------

መጠይቅ የተጀመረበት ሰዓት-----------

መጠይቅ ያለቀበት ሰዓት---------------

|  | | | | **ክፍል አንድ፡ ስነ ማሀበራዊ መጠጥቅ** | | | | | | | | |  |  |
| --- | --- | --- | --- | --- | --- | --- | --- | --- | --- | --- | --- | --- | --- | --- |
| መለያ  ቁጥር | | | | ጥያቄዎች | | አማራጭ መልስ | | | | | | | እለፍ |  |
| 101 | | | | አሁን ዕድሜዎት ስንት ነዉ ? | | ሙሉ ቁጥር ዕድሜ…………………………….. | | | | | | |  |  |
| 102 | | | | የት ነዉ የሚኖሩት ? | | ገጠር ………………………………………….…1  ከተማ ……………………………………………2 | | | | | | |  |  |
| 103 | | | | በትዳር ዉስጥ ምን ያክል ጊዜ ቆይተዋሉ? | | ሙሉ ዓመት/ወር…………………………… | | | | | | |  |  |
| 104 | | | | የባለቤቶት ዕድሜ ስንት ነዉ? | | ዕድሜን በሙሉ ቁጥር…………………………… | | | | | | |  |  |
| 105 | | | | ሀይማኖቶት ስንት ነዉ? | | ፕሮቴስታንት .........................................................1  ኦርቶዶክስ.............................................................2  ሙስሊም ..............................................................3  ካጦሊክ ..............................................................4  ሌላ , ይገለጽ.........................................................5 | | | | | | |  |  |
| 106 | | | | የባላቤቶት ሐይማኖት ነዉ? | | ፕሮቴስታንት .........................................................1  ኦርቶዶክስ.............................................................2  ሙስሊም ..............................................................3  ካጦሊክ ..............................................................4  ሌላ , ይገለጽ.........................................................5 | | | | | | |  |  |
| 107 | | | | ብሄሮት ምንድነዉ? | | ሀዲያ.................................................................1 ክምባታ.............................................................2  ስልጤ................................................................3  ጉራጌ.................................................................4  ሌላ, ይገለጽ......................................................5 | | | | | | |  |  |
| 108 | | | | የባለቤቶት ብሔር ምንድነዉ? | | ሀዲያ.................................................................1 ክምባታ..............................................................2  ስልጤ................................................................3  ጉራጌ.................................................................4  ሌላ, ይገለጽ......................................................5 | | | | | | |  |  |

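### Sections 6.16 and 6.21 put the questionnaire into Hadiyisa, while section 6.22 and the annexed translations use Amharic, so the version that measures the primary outcome need not be the one that passes the 6.16 checks

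*Protocol*

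**What the plan says.** Three sections of the protocol describe translation of the questionnaire.

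- **Section 6.16:** "Bilingual translators will translate the instruments into Hadiyisa". Then: "The instruments will be translated back into English by two bilingual translators from the Department of Hadiyisa, Wachemo University". Items are rated for comparability from 1 to 7, with the rule "There will be a formal evaluation of the translation for any mean score greater than 3". Next: "Pilot testing of the translated tool will be conducted among 27 couples who will not be included in the actual trial". Internal consistency is judged against a Cronbach's alpha of 0.7. The section closes by saying that the questionnaires are used at baseline and at completion.
- **Section 6.21:** the English questionnaire "will be translated into the local language (Hadiyisa) by fluent speakers" and is then back-translated. No rating or pilot is described here.
- **Section 6.22:** "The questionnaire will be translated into an Amharic version and then back to English by translators who are blind to the original questionnaire". Reliability and validity tests follow, covering the IPV items among others, and a pre-test in a kebele outside the study.

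The annexes hold English forms (Annexes II and III) and two translated forms, both Amharic: "Annex VI: የአማርኛ መጠይቅ (የምስት" for wives and "Annex vii: የባሎች መጠይቅ -አማርኛ ትርጉም" for husbands. Section 6.18 requires interviewers to speak both languages. A choice of language by participant preference is given only for the education manual (Appendix-iv, Language).

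**The concern.** The primary outcome is self-reported and act-based. Under section 6.17 a woman is counted as exposed if she says yes to at least one listed act, so the wording of each act decides case status. The formal translation checks belong to a Hadiyisa form, while 6.22 and the annexes point to an Amharic one. If the Amharic form is fielded, wholly or in part, the 6.16 checks may have been carried out on a different instrument. The secondary outcomes (knowledge, attitude, controlling behaviour, autonomy, self-efficacy) come from the same questionnaires and share the problem.

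**Working it through.** No figure in the plan needs reproducing. The check is a comparison of text.

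**1. Which language, and which checks?**

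| Source | Target language | Checks described |
|---|---|---|
| 6.16 | Hadiyisa | Blind back-translation, 1–7 rating, pilot in 27 couples, alpha threshold 0.7 |
| 6.21 | Hadiyisa | Back-translation |
| 6.22 | Amharic | Blind back-translation, reliability and validity tests, pre-test |
| Annexes VI and vii | Amharic | None stated in the annex |

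No section says that two versions will be used, how an interviewer would choose, or that both pass through 6.16.

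**2. Do the annexed versions agree?** I compared the Amharic forms with the English ones.

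- *Autonomy (wives).* English codes: 2 = together, 3 = husband alone. Amharic codes: 2 = husband alone, 3 = together. Section 6.17 scores a joint decision 1 and a husband-only decision 0, summed over five items. A woman who decides jointly on all five is recorded as code 3 on the Amharic form. Scored correctly she gets 5 × 1 = 5; read with the English key she gets 5 × 0 = 0.
- *Physical violence, third act (wives).* The English item asks about a fist or another object that could hurt. On my reading, the Amharic item uses the word that the first item uses for a slap. The Amharic handout (Annex ix) words the same act with the hand instead. A native speaker should confirm this.
- *Knowledge (husbands).* English item 208 is about restricting contact with family or friends. The corresponding Amharic item 408 is about adverse maternal and newborn outcomes. Good knowledge needs 75% of nine items: 0.75 × 9 = 6.75, so 7 correct. One differing item can move a man across that line.
- *Attitude (husbands).* Section 6.17 lists five scenarios. The Amharic form has all five. The English form repeats the first and omits the burnt-food scenario, so it covers four. Here the English form is the one that departs from 6.17.

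The women's IPV block has the same number of acts in both languages: 6 physical, 4 psychological and 3 sexual.

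**3. What would misclassification do?** If a form has sensitivity Se and specificity Sp, equal in both arms, a true prevalence p is observed as p·Se + (1 − p)(1 − Sp). The observed difference between arms is the true difference times (Se + Sp − 1). Any such error shrinks the difference, but the documents give neither Se nor Sp for either version, so no size follows.

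**The case against.** The best defence is that Hadiyisa is plainly the main plan. Two of the three sections name it, 6.16 says its questionnaires are used in both rounds, and Figure 7 ends in field work. The Amharic sentence in 6.22 could be a slip, or could describe an additional version. An Amharic form would also not go untested, since 6.22 promises blind back-translation, reliability and validity tests and a pre-test.

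Much of this stands. It does not settle which form is used: a slip in one sentence does not explain two complete Amharic questionnaires in the annexes, and 6.22 does not repeat the comparability rating or the alpha threshold.

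The defence also limits what may be inferred. A reader might conclude:

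- that interviewers will translate Amharic forms aloud on the spot. No section says so.
- that the Amharic version is unvalidated. Section 6.22 promises tests of its own.
- that errors will cluster by kebele. Section 6.18 gives ten data collectors and does not allocate them to kebeles.
- that a definite amount of power is lost. Any such figure needs an assumed sensitivity and specificity, an assumed accuracy for the form it is compared with, and an assumption on how the intracluster correlation (0.05 in section 6.8) changes under error. The documents supply none of these three.
- that no Hadiyisa form exists. Some pages at the end of the protocol were not in the text available, so only its absence from that text can be stated.

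**Conclusion.** The contradiction holds and no passage reconciles it. As written, the version that measures the primary outcome need not be the one that receives the 6.16 rating, pilot and reliability check. This is more than loose wording, because the annexed versions already disagree on response codes, on one act in the primary outcome (subject to a native speaker's confirmation) and on husbands' items.

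The consequence is a risk of misclassification in both arms. The same questionnaires are planned for both groups, so a between-arm bias, which a reader might infer, is not shown. The size cannot be derived from the documents. The fist item may matter little for the composite, since another act can still classify the woman as exposed. The autonomy inversion arises only if answers coded on one form are read with the other form's key. The conflict between 6.16 and 6.21 on one side and 6.22 on the other does not depend on the annexes. The sponsor should correct it, because the outcome instrument is affected and the remedy is cheap.

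**What to change.** 1. Make sections 6.16, 6.21 and 6.22 name the same fielding language or languages.
2. Apply the 6.16 back-translation, rating, pilot and reliability steps to every version that is fielded, and annex that version.
3. Align response codes and items across all versions with the English forms and with section 6.17. Where the English form departs from 6.17 (the husbands' attitude items), correct the English form too.
4. If two languages are fielded, state how one is chosen, record the interview language in KoBo, and use the same language for a respondent at baseline and endline.

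If one language is kept, the cost is text alignment in three sections, corrections to the forms and, for Hadiyisa, annexing a form that 6.16 already plans. If both are kept, add one KoBo field and the 6.16 steps for the second version.

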**6.23 Data Management**

**Qualitative data**: Data transcription and translation will be carried out on the field while the data collection is being conducted. An audio recording of the interview will be transcribed immediately after the interview. The transcription will be translated into English on the same day as the interview. The translation will be read line-by-line for a deep understanding of the data.

**Quantitative Data:** Regular supervision and follow-up will be done by supervisors and the principal investigator. A regular check-up of the data will be made on a daily basis by supervisors. Every day, data collected by KoBo Collect (the mobile application) will be checked for completeness and consistency before being sent to the server (KoBo Toolbox). The supervisor and principal investigator will consider the following points during the checkup of the collected data: the length of time to finish each survey, the collection of Global Positioning System (GPS) points, and their random distribution. Trial participants who are loss to follow up will be listed along with their reasons. Only the study team will have access to the data set. The anonymous record and coding of personal data will not be disclosed to any third party to ensure strict secrecy. Data will be stored on a password-protected data server (KoBo Toolbox) and only accessible by the research team.

**6.24 Data processing and analysis**

**Qualitative Data:** The complete data will be exported to ATLAS Ti. 7.0 for data analysis. The codes will be created initially by independent coders. The codes will be merged after discussion to reach consensus codes. At least two coders will be involved in the coding process and categorization of the codes. These codes will be merged into larger categories and then set into sub-themes. Sub-themes will be reviewed further to develop overarching themes**.** Then the data will be summarized and reported with some important direct quotes.

**Quantitative data:** A complete questionnaire with individual code and specific cluster will be exported from server to SPSS or STATA for analysis. At baseline, descriptive statistics such as proportions, percentages, tables, diagrams, and figures will be used to describe the study population at the intervention and control arms before the intervention starts. The baseline characteristics of the participants and their prior exposure to intimate partner violence will be examined and compared between the intervention and control groups. The chi-square test and independent sample t-test will be used to compare the baseline characteristics for categorical and continuous variables, respectively. After the end-line survey, the proportion of women who experienced intimate partner violence during the trial period will be calculated with a corresponding confidence interval.

We will use the McNemar test to appreciate the differences in outcomes of interest in both intervention and control groups before and after the intervention for categorical data. A paired t-test will be used to compare continues outcome of interest in the intervention and the control groups after and before the intervention. A model of longitudinal data analysis, the GEE (Generalized Estimating Equation), will be used to test the independent effect of the intervention on the outcome of the interest. Data analysis will be performed with an intention-to-treat analysis approach. During the analysis, the effect size, confidence interval, and p-value will be calculated. A model with the smallest Quasi-likelihood under the Independence Model Criterion (QIC) will be used to select the best-fitted model. All tests will be two-sided, and statistical significance will be declared at p < 0.05.

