**6.8 sample size**

**Qualitative study:** the sample size for a qualitative study will be determined by information saturation (Dworkin, 2012). But, for planning purposes, eight (8) Focus Group Discussions (FDG)( at least two FGDs from male partners (husbands of pregnant women), two FGDs from religious leaders, two FGDs from community leaders, and two FGDs from the women's development army) will be considered. Moreover, six in-depth interviews (IDI) among pregnant women and 70**participants** will be involved in FGD, and IDI will be involved in order to explore community perspectives towards IPV in pregnancy.

**Quantitative study (CRCT):** sample size is calculated by using the following parameters: The prevalence of IPV during pregnancy (p) was  37.5% in a study conducted in Tigray, Ethiopia (Adhena et al., 2020). The expected decline of IPVp following the intervention will be 20%, with 80% power, a 95% confidence interval, an intra-correlation coefficient (ICC) variation of 0.05, a loss to follow-up of 20%, and a design effect of 2.3. Hence, the sample size is based on Stata version 16.

Design Effect (DE) = 1 + ρ (m-1)

Where,

DE=Design effect,

ρ= intra-cluster correlation coefficient = 0.05

m=number of participants per cluster = 27.

DE=1+0.05(27-1) =2.3

Attrition (20%)

=216 couples per control group and 216 couples per intervention group; sample size =432 couples, making a total of 864 participants.

Total cluster (k) = 16 kebeles (clusters)

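### The trial is randomised and sized by kebele, but no outcome test in the analysis section is tied to the kebele, and the two before/after tests do not compare the arms

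*Protocol*

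**What the plan says.** Section 6.12 makes the kebele the unit of randomisation, with 8 kebeles per arm. Section 6.8 carries this into the sample size: "an intra-correlation coefficient (ICC) variation of 0.05, a loss to follow-up of 20%, and a design effect of 2.3", worked out as "DE=1+0.05(27-1) =2.3".

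Section 6.24 (Data processing and analysis), repeated in shorter form in the Summary, gives the tests:

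- Categorical outcomes, before against after: "We will use the McNemar test to appreciate the differences in outcomes of interest in both intervention and control groups". A paired t test does the same for continuous outcomes.
- Effect of the intervention: "A model of longitudinal data analysis, the GEE (Generalized Estimating Equation), will be used to test the independent effect of the intervention".
- Choice of model: "A model with the smallest Quasi-likelihood under the Independence Model Criterion (QIC) will be used to select the best-fitted model".
- Threshold: "All tests will be two-sided, and statistical significance will be declared at p < 0.05".

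The section also promises an intention-to-treat approach. It mentions the cluster once, as a code exported with each questionnaire. It does not say that any model uses that code.

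**The concern.** The design pays for clustering by multiplying the sample by 2.3, yet the analysis section does not say where that clustering enters a test.

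Three of its choices are stated outright and are not merely details left open:

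- **McNemar and paired t.** They treat women in the same kebele as independent. They test change within one arm, whereas the hypotheses in section 5.2 compare the arms. They also need both measurements, so a woman without an endline interview drops out, although 20% loss is planned and intention-to-treat is promised.
- **The GEE.** Calling it longitudinal reads most naturally as repeated measures grouped on the woman. That grouping handles the baseline-endline correlation but not the correlation between women in one kebele.
- **Smallest QIC.** The data choose the model that produces the primary result.

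At stake is the meaning of p < 0.05 for the primary outcome. There is also a risk that a significant fall in the intervention arm beside a non-significant one in control is reported as an effect, although no comparison of arms has been made.

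**Working it through.** **Inputs from the protocol.** Control prevalence: "was 37.5% in a study conducted in Tigray, Ethiopia". Cluster size: "m=number of participants per cluster = 27". ICC 0.05, design effect 2.3, 20% loss, 16 kebeles (8 per arm), two-sided 0.05, power 80%.

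**1. The protocol's own figure.** The 20% decline reproduces the sample size only when read as 20 percentage points, 37.5% to 17.5%. The two-proportion formula with pooled variance gives 78 per arm. Then 78 × 2.3 = 179.4, and 179.4 × 1.2 = 215.3, rounded up to the stated 216. The design effect was therefore really used. The size of the effect plays no part in the error rates below.

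**2. Kebele ignored in an endline comparison of arms.** The true variance is DE times what the test assumes, so the error is 2 × [1 − Φ(1.96/√DE)].

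- m = 27: DE = 1 + 0.05 × 26 = 2.3; 1.96/√2.3 = 1.292; error = 19.6%. Beta-binomial simulation (20,000 runs) gives 19.7%.
- m = 27 × 0.8 = 21.6 after 20% loss: DE = 2.03; error = 16.9%. Simulation gives about 17-17.5%.
- m = 27 with other ICCs: ICC 0.01 gives DE 1.26 and 8.1%; ICC 0.10 gives DE 3.6 and 30.2%.

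**3. Kebele used, ICC 0.05, 8 kebeles per arm, no true effect.**

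| Endline test | Simulated two-sided error |
|---|---|
| Kebele-level GEE, uncorrected sandwich, z | 8.4-8.7% from the closed form; 8.9% (1,500 runs) and 6.8% (600 runs) from simulated GEE analyses |
| Same, with t on 14 df | 6.1% |
| Kebele-level GEE, bias-reduced sandwich, z | 5.1% (1,500 runs); 4.3% (600 runs) |
| Same, with t on 14 df | 3.2% (600 runs) |
| Kebele-level t test, 14 df | 4.6-5.1% |

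The Monte Carlo standard error with 600 runs is roughly one percentage point.

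**4. Tests that use both time points.** The result depends on how far the kebele effect persists from baseline to endline. The protocol does not give this, so the autocorrelation of the kebele effect is assumed.

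| Assumed autocorrelation | McNemar within one arm, no true change | Arm-by-time contrast, GEE grouped on the woman |
|---|---|---|
| 1.0 | 5.2% | 5.4-5.7% |
| 0.8 | 10.0% | 9.9-10.4% |
| 0.5 | 16.7% | 15.3-18.1% |
| 0 | 24.5% | up to about 26% |

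If the GEE is grouped on the woman but the contrast is between arms at endline, the error is about 19-20% whatever the autocorrelation, as in step 2. An arm-by-time contrast grouped on kebele with an uncorrected sandwich and z gives 8.6-9.6%.

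The McNemar column is the error for a claim of change within one arm. It is not an error rate for the effect of the intervention.

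**The case against.** The strongest reply is that the protocol assigns the test of the intervention to the GEE and nowhere says that this GEE ignores the kebele. A baseline-endline GEE can be grouped on kebele, and the cluster code is in the exported data. Variance estimator and small-sample correction are commonly left to a statistical analysis plan, and one may exist that was not available here. McNemar is offered only to describe before/after differences, and the protocol does not say that conclusions will rest on it.

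Much of this stands, and it rules out several stronger readings:

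- A reader might infer that the planned analysis has a false-positive rate of 9-20%. The protocol fixes neither grouping unit nor variance estimator, so no single rate or range belongs to the plan.
- A reader might count the chi-square and independent t tests among the faulty outcome tests. Section 6.24 assigns them to baseline characteristics only, so they do not affect the error for the intervention effect.
- A reader might blame QIC for part of the inflation. Nothing calculated here shows that. Its fault is that the primary model is not fixed before the data are seen.
- A reader might take intention-to-treat to be violated throughout. The loss of incomplete pairs concerns McNemar and paired t; the protocol does not say that the GEE excludes those women.

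The reply does not remove the mismatch. McNemar and paired t are named for the outcomes of interest, under a blanket p < 0.05 rule, with no allowance for clustering. The one phrase describing the GEE points towards the woman as the unit. A later analysis plan could supply the kebele and a correction, but it could not drop the within-arm tests or the QIC rule without departing from the protocol.

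**Conclusion.** The point holds in conditional form: the sample size uses the kebele, and no stated outcome test does. At ICC 0.05 with 8 kebeles per arm, the two-sided error of an endline comparison is about 20% if the kebele is ignored (about 17% at 22 women per kebele), about 7-9% with a kebele-level GEE using an uncorrected sandwich and z, and about 5% with a kebele-level t test on 14 df. For a woman-level arm-by-time GEE, or McNemar within one arm, it runs from about 5% to 25%, depending on an unstated stability of the kebele effect over time.

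The figures assume the protocol's ICC and equal kebele sizes. A smaller ICC shrinks the problem without removing it: ignoring the kebele still gives about 8% at ICC 0.01. Because the primary inference is affected and the remedy is only wording, this should be settled before the data are analysed.

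**What to change.** In section 6.24, and to match in the Summary:

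1. Name one primary test: the endline IPV outcome compared between arms by a GEE with kebele as the cluster, adjusted for the woman's baseline IPV, with a small-sample correction for 16 clusters. A bias-corrected sandwich error is one choice and t on 14 df is another. In the simulations the t reference alone still left about 6%, and a bias-reduced sandwich combined with t was somewhat conservative at about 3%.
2. Check the result with a kebele-level t test on 14 df.
3. Use the same model form for the secondary outcomes.
4. Report before/after change within each arm descriptively, and draw no conclusion from McNemar or paired t p-values.
5. Fix the covariates and working correlation of the primary model in advance, in place of selection by smallest QIC.

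The cost is analysis wording. The kebele code is already exported with each record, and a cluster-summary t test needs no special software. Confidence intervals will be wider than those from an analysis that ignores the kebele.
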